### Covariates

If dropout is associated with other variables, these variables will be added as predictors to reduce bias. Baseline differences between groups will be examined (e.g., demographics); however, these tests will not be used to select covariates in the primary intent-to-treat analysis. Instead, the potential influences of baseline differences will be evaluated as moderators. The stratification factor (age) will be included as a covariate, per recommendations [151]. Additional covariates may be included if they are associated with the outcome but not the predictor/s. Sex will be included as a covariate in sleep-related outcomes, given the substantial body of literature identifying sex-related differences in sleep problems [80, 152–154]. Presence of OSA and adherence to OSA treatment are likely to influence sleep-related outcomes and will be included as covariates in analyses with these outcomes. Presence of OSA will be dummy-coded as mild and moderate/severe with no diagnosis as the reference group. Adherence to OSA treatment will be dummy-coded as yes with no as the reference group.

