The “platform” through which we will continue studying the MSI is a psychological treatment for sleep and circadian problems. This focus was selected because sleep and circadian disturbance is common among midlife and older adults [40–42]. For example, healthy aging is associated with decreases in total sleep duration, decreased sleep efficiency, increased sleep latency, and more frequent nighttime awakenings [43, 44]. Untreated sleep and circadian problems also have critical negative consequences including an increased risk for new onset of psychiatric and medical illness [45], increased accidents [46, 47], increased fall risk [48–50], increased chronic pain [51], and reduced physical activity [52].

Cognitive behavior therapy for insomnia (CBT-I) has been demonstrated to be an effective treatment for insomnia among midlife and older adults [53, 54] while also improving the symptoms of comorbid physical and mental disorders [55–58]. However, midlife and older adults experience a broader range of sleep and circadian dysfunctions (e.g., advanced circadian phase, medical problems, sleep apnea). To address this broader range, the current research will focus on the Transdiagnostic Sleep and Circadian Intervention (TranS-C) [59] as it incorporates the components of CBT-I, but also includes a range of content related to other sleep and circadian problems experienced by midlife and older adults. TranS-C is a modular, skills-based approach that is transdiagnostic in that it has been designed to address a range of sleep and circadian problems for a range of mental and physical disorders. Interestingly, in prior research, older people had a poorer response to TranS-C relative to younger people [60]. In another study limited to midlife and older adults, TranS-C was associated with improvements in many outcomes (depression, sleep disturbance, sleep health, and select sleep/wake outcomes), but not all improvements were sustained at follow-up [61]. The present study tests whether adding the MSI to TranS-C may further improve outcomes for midlife and older people.

Previous research has also demonstrated other sub-groups that have a poor response to treatment including individuals with fewer years of education [24, 62, 63], poorer baseline cognitive functioning [64, 65], and greater baseline symptom severity [66]. We will also examine if these poor response sub-groups will derive a particular benefit from adding the MSI to TranS-C.

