### Statistical methods for primary and secondary outcomes {20a}

#### Aim 1: Efficacy of TranS-C + MSI compared to TranS-C alone

Hierarchical Linear Modeling (HLM) [146–148] will be used to test for differences in the trajectories of primary and secondary outcomes across time between the two treatment groups (TranS-C + MSI vs. TranS-C alone). All primary and secondary outcomes are continuous variables (see Table 1) and will be analyzed using the same approach. The 1st level will represent within-person variation and will include dummy-coded time indicators as the predictor (0 = pre-treatment, 1 = post-treatment, 2 = 6FU, 3 = 12FU). The 2nd level will represent between-person variation and will include dummy-coded treatment condition (0 = TranS-C alone, 1 = TranS-C + MSI) and treatment-by-time interaction terms as the predictor. Interactions between treatment condition and the time indicators will be retained only if found significant at the 5% level. A significant interaction between treatment condition and time indicators would suggest that there are different trajectories across time between the two treatment conditions and will be graphed to interpret the interaction. Significant interactions will be interpreted with planned contrasts to assess if treatment effects change over time.

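### When the Aim 1 treatment-by-time interaction is retained, age stratum, sex and OSA entered as main effects do not adjust the post-versus-pre treatment contrast

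*Protocol article*

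**What the plan says.** Protocol article, Covariates: "The stratification factor (age) will be included as a covariate, per recommendations". This applies to every outcome. "Sex will be included as a covariate in sleep-related outcomes", and OSA presence and adherence to OSA treatment "will be included as covariates in analyses with these outcomes", again meaning the sleep-related ones. Variables associated with dropout are also to be added as predictors, to reduce bias. No interaction between any of these and time is described.

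Protocol article, Aim 1 under Statistical methods {20a}: the hierarchical linear model is meant to "test for differences in the trajectories of primary and secondary outcomes across time between the two treatment groups". Time enters as four indicators with pre-treatment as the first, so the pre-treatment score is an outcome rather than a covariate. The person level contains treatment condition and "treatment-by-time interaction terms as the predictor". There is also a retention rule: "Interactions between treatment condition and the time indicators will be retained only if found significant at the 5% level".

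Protocol article, Background {6a}: in prior research "older people had a poorer response to TranS-C relative to younger people". Sequence generation {16a} stratifies by age because of its possible influence on sleep, on treatment outcome, or on both. It gives the absence of any known sex difference in response as the reason for not stratifying by sex.

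**The concern.** The covariates are there so that the treatment effect is adjusted for the stratification factor and for variables expected to influence sleep. In this model the effect of interest is a difference between arms in change from pre-treatment. A main effect of a fixed characteristic describes level, and level drops out of change. To carry an effect on change, such as the poorer response of older people, into the tested contrast, the covariate has to be crossed with time.

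On the natural reading of the Covariates section, the trial would report an Aim 1 contrast as adjusted for age (and, for PROMIS-SD, for sex and OSA) when it is numerically the unadjusted one, or very nearly so. Chance imbalance in factors that affect change would stay in the estimate, and whatever precision those factors could supply would not be used.

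**Working it through.** **Inputs from the protocol.** 1:1 allocation; four waves; maximum likelihood; N = 178, which reproduces as 148 × 1.2 = 177.6, rounded up. The protocol gives no figure for the effect of covariate adjustment, so there is none to reproduce. Correlations, prevalences and covariate effects below are assumptions.

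**Step 1, algebra.** Let the mean at wave t be a_t + b_t × (treatment) + g × x, with x fixed over time. Let D_t be the raw arm difference at wave t and Dx the arm difference in x. With complete data and the full treatment-by-time structure, the fitted arm difference is D_t − g·Dx. The post-versus-pre contrast is

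(D_post − g·Dx) − (D_pre − g·Dx) = D_post − D_pre.

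The term in g cancels for any covariance matrix. The residual of the change score contains no g either, so the standard error is the same.

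**Step 2, fitted models.** Simulated data, N = 178, four waves, complete data, age, sex, OSA and adherence as main effects (post-treatment interaction, ML):

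| Model | No covariates | Main-effect covariates |
|---|---|---|
| Random intercept | −0.4094 (SE 0.1304) | −0.4094 (SE 0.1304) |
| Random slope | −0.4641 (SE 0.1305) | −0.4641 (SE 0.1305) |
| Unstructured | −0.3047 (SE 0.1347) | −0.3047 (SE 0.1347) |

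Over 150 data sets (random intercept) the largest change in the estimate was 4e-14 and in the SE about 1e-5 in relative terms, which is optimiser noise.

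**Step 3, dropout.** In a separate simulation with 20% dropout, the SE changed by about 0.0001 and the estimate by at most 0.03 SD in any trial. Two single data sets with 71% and 81% observed at 12FU moved from −0.4248 to −0.4213 (SE 0.1380 to 0.1371) and from −0.2763 to −0.2736 (SE 0.1364 to 0.1363).

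**Step 4, what time interactions would buy.** Assume unit SD and correlation 0.5, so the variance of change is 2(1 − 0.5) = 1. Assume 30% aged 70 or over, 40% with OSA and 65% female (the protocol's recruitment target), shifting change by 0.4, 0.4 and 0.2 SD. Variance added to change if these are left out:

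- age: 0.4² × 0.3 × 0.7 = 0.0336
- OSA: 0.4² × 0.4 × 0.6 = 0.0384
- sex: 0.2² × 0.65 × 0.35 = 0.0091
- total: 0.0811

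SE of the contrast with all three crossed with time: √(1 × 4/178) = 0.150. Without: √(1.0811 × 4/178) = 0.156. The ratio is √1.0811 = 1.040, or 4%. Simulation of 400 trials gave 0.1490 against 0.1555; (0.1555/0.1490)² = 1.09, worth about 16 participants, with the estimate moving 0.036 SD on average as chance imbalance was removed. One data set with covariate effects on change gave −0.3047 (SE 0.1326) with main effects and −0.3238 (SE 0.1262) with time interactions, about 5% smaller. Age alone, which is all that SDS and SWLS receive: √1.0336 = 1.017, or 1.7%. With no effects on change there is no gain; in one such data set the SE went from 0.1304 to 0.1309.

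**Step 5, predictors of dropout.** With age shifting change by 0.4 SD and deliberately extreme dropout among older participants, bias in the post-treatment contrast (SD units) was:

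| Dropout of older participants, by arm | No covariate | Main effect | Age-by-time |
|---|---|---|---|
| 50% vs 0% | −0.08 | −0.05 | −0.01 |
| 40% vs 10% | −0.04 | −0.02 | 0.00 |

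With equal dropout there was no bias under any model.

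**Step 6, where the covariates do work.** If the interaction is dropped under the retention rule, the treatment term is a main effect: over 150 data sets adjustment moved it by 0.058 on average and lowered its SE by about 13%. An arm difference at the post-treatment visit alone went from −0.2004 (SE 0.1553) to −0.2115 (SE 0.1344).

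**The case against.** The strongest reply is that a journal article saying a variable is a covariate does not rule out covariate-by-time terms; in a two-level model a person-level variable may predict the intercept, the time terms or both. This stands as far as it goes: nothing excludes such terms. But the only interaction that the Aim 1 model names is treatment with time, so main effects are the natural reading, and the text should settle it.

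A reader might infer that the planned adjustment achieves nothing anywhere. The documents do not support that. It acts when a non-significant interaction is removed (the post-treatment interaction was non-significant in 36% of the simulated data sets, under their assumptions), in an arm contrast at a single visit, for the memory outcomes, which Table 2 shows without a pre-treatment wave, and in the Aim 2 models of outcomes at single timepoints. With complete data, however, the test that decides retention is itself untouched by the covariates.

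Nor is the rationale for the covariates solely about response. The stratification rationale covers sleep as well as treatment outcome, and the reason given for sex concerns differences in sleep problems, which is level. Since the protocol knows of no sex difference in response, the 0.2 SD sex effect assumed above has no support in it; the OSA effect and prevalence are also unsourced.

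Finally, the Covariates section evaluates baseline differences as moderators, and age is an Aim 3 moderator. Those analyses address effects on response but do not adjust the primary contrast.

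**Conclusion.** The point holds for the retained Aim 1 interaction. There, main-effect covariates leave the post-versus-pre contrast and its SE exactly unchanged with complete data and almost unchanged under about 20% dropout.

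It would be wrong to conclude that the test is biased or its type I error inflated: under randomisation with complete data it is not. It would also be wrong to say that main effects do nothing for predictors of dropout; they correct part of the bias when dropout differs by arm, and time interactions correct nearly all of it.

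The cost of leaving the plan as it is lies in modest precision and uncorrected chance imbalance: about 1.7% in the SE for age alone, 4–5% for all covariates if the assumed effects on change hold, and nothing if there are none. Sex and OSA bear on only one of the three primary outcomes, PROMIS-SD. The change is worth making because it is cheap and makes the stated stratification adjustment act on the contrast that is tested.

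**What to change.** In the Covariates section, state that in the Aim 1 models the age stratum (all outcomes), OSA presence and OSA treatment adherence (sleep-related outcomes), and any pre-randomisation predictor of dropout that is added, enter together with their interactions with the time indicators, and without interactions with treatment. Sex-by-time is optional, given the protocol's statement on sex and response. A model with the pre-treatment score as a covariate would be another way to make the covariates act on the effect.

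The cost is wording plus three parameters per covariate term at N = 178: 3 for SDS and SWLS (age), and 12 for PROMIS-SD (age 3, two OSA indicators 6, adherence 3), or 15 with sex. If the covariates do not affect change, those parameters buy nothing. The change should be fixed before the data are analysed by arm.

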### Plans to give access to the full protocol, participant-level data, and statistical code {31c}

Following data collection, de-identified data will be made through the Analysis, Visualization, and Informatics Lab-space (AnVIL).

## Oversight and monitoring

### Composition of the coordinating center and trial steering committee {5d}

This trial is supervised by the principal investigator ([name]), who manages the assessment team, therapists, and the data management team. The principal investigator will meet with members of each team as needed in addition to daily email communication. The responsibilities of each team member are detailed elsewhere in this protocol. In sum, the assessment team will be responsible for the informed consent process and conducting assessments. Therapists are responsible for delivering TranS-C + MSI or TranS-C alone. The data management team will be responsible for downloading, collating, and analyzing the data. There is no coordinating center, trial steering committee, or Stakeholder and Public Involvement Group. The trial sponsor is University of California, Berkeley. Other than ethical approval for the study, the sponsor has no role or ultimate authority in study design; collection, management, analysis, or interpretation of the data; writing of the report; or the decision to submit the report for publication.

### Composition of the data monitoring committee, its role and reporting structure {21a}

A Data Safety Monitoring Board (DSMB) has been formed to monitor participant safety, evaluate the progress of the study, to review procedures for maintaining the confidentiality of data, and the quality of data collection, management, and analyses. The board includes members with expertise in sleep, older adults, basic science, and statistics. Members are independent from the principal investigator and competing interests. A report will be made to the board bi-annually for the first year of the research. In subsequent years, reports will be made to the board annually. However, if safety issues arise, monthly meetings will be conducted. Each report will include a detailed analysis of the study’s progress including the number of participants screened, the number of participants entered, the number of participants dropping out with the reasons for discontinuing, participant descriptive information, and the number of adverse or serious events. Interim analyses will not be conducted.

### Adverse event reporting and harms {22}

In this trial, adverse events (AEs) and serious adverse events (SAEs) are not expected and there is no biological plausibility for this intervention to cause any NIH-defined serious events such as hospitalizations, deaths, or disability. However, these events can occur within the trial population, but they are not anticipated to be related to the trial. Potential harms of treatment may arise from the sleep restriction and stimulus control components of TranS-C, which have been associated with a small amount of short-term sleep deprivation, increased sleepiness, and a deterioration in functioning [155, 156]. Actigraphy can cause minor skin irritation from the watch band, but this is rare. WatchPAT, which screens for sleep apnea, may cause transient psychological distress in some participants, but this is rare. The method for assessing adverse events (AEs) follows prior research [126, 127]. A trained assessor will administer a checklist to patients to systematically assess for possible AEs at the post-treatment assessment. The checklist will screen for unwanted symptoms following treatment and for each endorsed symptom several follow-up questions will be asked (for details, see “Adverse events checklist” under Outcomes). Furthermore, adverse events related to treatment will be assessed by therapists non-systematically throughout treatment. SAEs that are unexpected will be reported to the IRB, NIA program officer, and to the independent DSMB within 48 h of the study’s knowledge of the SAE. All AEs will be reported in future publications, including their nature, severity (mild, moderate, severe), and the relationship to the trial (related, not related).

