Promisingly, however, the impact of memory failures can be minimized at both the encoding and retrieval stages through the use of memory support strategies, which have been shown to be effective at improving memory in individuals with depression and Alzheimer’s disease [13–15]. Building on this prior research, the Memory Support Intervention (MSI) was developed to improve patient memory for treatment contents with the aim of improving patient outcomes [16]. In line with the Experimental Therapeutics Approach [17, 18], the MSI was designed to engage a target mechanism of change, *patient memory for treatment*, which is proposed to mediate patient outcomes [16]. The intervention was designed to improve memory for treatment contents rather than to improve general memory functioning. The original MSI consists of eight different memory supports that were derived from education and cognitive psychology research [19–22]. Four of the memory support strategies are *constructive*, defined as supports that prompt patients to generate new ideas, inferences, or connections in relation to treatment content. The other four memory support strategies are *non-constructive* and highlight aspects of treatment without asking patients to generate anything new related to it [16, 23]**.**

In a small pilot study (*n* = 48), adults with major depressive disorder (MDD) were randomized to receive either cognitive therapy plus the Memory Support Intervention (CT + MSI) or cognitive therapy as usual (CT-as-usual) [24]. Patient memory for treatment contents was enhanced in the CT + MSI condition relative to CT-as-usual at post-treatment with a small to medium effect size. Results from a confirmatory efficacy trial (*N* = 178) where patients diagnosed with MDD were also randomized to CT + MSI or CT-as-usual found improvements in the CT + MSI condition relative to CT-as-usual on only two secondary outcome measures: (1) lower depression severity at 6-month follow-up and (2) a greater reduction in unhealthy days from pre-treatment to 6-month follow-up [25]. A secondary analysis of this trial assessed differences at 12-month follow-up and did not find any significant differences in outcomes between the two treatment conditions [26].

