**Patient**									
Demographic Form	x								
Adapted Brief Disability Questionnaire	x								
Montreal Cognitive Assessment	x								
SCISD^a^	x	x							
WatchPAT	x								
Additional Eligibility Items	x								
PROMIS-SD	x	x					x	x	x
PROMIS-SRI		x					x	x	x
Sleep Health Composite		x					x	x	x
Sleep Diary		x					x	x	x
Actigraphy		x					x		
Sheehan Disability Scale		x					x	x	x
WHODAS 2.0	x	x					x	x	x
Epworth Sleepiness Scale	x	x					x	x	x
Satisfaction with Life Scale		x					x	x	x
PANAS		x					x	x	x
Patient Treatment Recall Task				x			x	x	x
Thoughts and Applications Task				x			x	x	x
Cognitive Failure Questionnaire		x					x	x	x
Credibility and Expectancy			x						
Utilization Scale		x					x	x	x
Adverse Events Checklist							x		

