### Other participant measures

#### Adverse events

The method for assessing adverse events (AEs) follows prior research [126, 127]. A trained assessor will administer the adverse events checklist to clients to assess possible AEs at the post-treatment assessment. *Examples of the questions to be asked are:* I’m going to go through a list of symptoms please let me know whether the sleep changes you made during the sleep coaching treatment that interfered with your normal functioning in anyway? Is the [negative effect] still present? What makes you think that [negative effect] was related to a treatment you received in this study? Then the participant is asked to rate the frequency, intensity and interference caused by the [negative effect] for the past week. Examples of symptoms assessed include low mood, extreme sleepiness, and worsening sleep.

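### The adverse-event collection described cannot fully supply the promised report of all AEs, classed as related or not related, or complete event counts for the DSMB

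*Protocol article*

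**What the plan says.** The output is stated in two places. Under Adverse event reporting and harms {22}: "All AEs will be reported in future publications, including their nature, severity (mild, moderate, severe), and the relationship to the trial (related, not related"). Under Composition of the data monitoring committee {21a}, each DSMB report is to include "participant descriptive information, and the number of adverse or serious events".

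The input comes by three routes.

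- **Checklist.** The Adverse events section under Other participant measures says: "A trained assessor will administer the adverse events checklist to clients to assess possible AEs at the post-treatment assessment". In Table 2 the row "Adverse Events Checklist" carries a single mark, at post-treatment. The example opening question is "please let me know whether the sleep changes you made during the sleep coaching treatment that interfered with your normal functioning in anyway", and an example follow-up is "What makes you think that [negative effect] was related to a treatment you received in this study". The harms section describes the same checklist as a systematic screen for unwanted symptoms after treatment and refers back to this description for detail.
- **Therapists.** "adverse events related to treatment will be assessed by therapists non-systematically throughout treatment".
- **Serious events.** Unexpected SAEs go to the IRB, the funder's program officer and the DSMB within 48 hours of the team learning of them. No relatedness condition and no end date are attached.

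**The concern.** A report that divides all AEs into related and not related needs collection that does not depend on suspected cause. The harms section itself accepts that hospitalizations, deaths and disability can occur in this population without being caused by the trial, so the not-related class is expected to have members. As described, the therapist route screens on relatedness before anything is recorded, and the questions shown for the checklist lead the participant to report effects that he or she links to the treatment. Nothing is actively asked after post-treatment, although participants are followed for 12 months from the start of treatment.

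At stake is the reading of the safety results. A published table headed as all AEs would under-count unrelated and later events, and the DSMB totals would carry the same gap. A short list of unrelated events could then be taken as evidence about the population when it partly reflects how the question was asked.

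**Working it through.** The plan gives no figure to reproduce here. The check sets the passages side by side and then works out how much of follow-up the scheduled collection covers.

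**1. Promise against routes**

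| Kind of event | Promised in {22} or {21a}? | Route described |
|---|---|---|
| Related, during treatment | Yes | Therapist (non-systematic); checklist |
| Unrelated and not serious, during treatment | Yes | Not the therapist route. Checklist if it works as a general symptom screen ({22}); doubtful if asked with the example wording (Adverse events section) |
| Not serious, after post-treatment | Yes, on a plain reading of all AEs | None scheduled |
| Unexpected and serious, at any time | Yes | Passive: reported if the team learns of it |

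The second row shows that the two descriptions of the checklist do not agree. The third row shows that the schedule does not reach as far as the promise. One harm named in {22}, skin irritation from the actigraph, illustrates this: under Plans for assessment and collection of outcomes {18a}, the second week of wear starts after the post-treatment assessment, which is when the only checklist is given.

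**2. Follow-up time covered by scheduled AE collection**

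Inputs, all from {18a}:

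- Treatment typically ends 8 to 10 weeks after it starts.
- The post-treatment assessment takes place 0 to 2 weeks after the last session.
- The follow-ups are dated from the start of treatment, so the last is at 12 months, taken as 52 weeks.

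Week of the checklist = treatment length + delay:

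- earliest: 8 + 0 = week 8
- latest: 10 + 2 = week 12

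Weeks with no scheduled AE question = 52 − week of the checklist:

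- 52 − 12 = 40 weeks; 40/52 = 77%
- 52 − 8 = 44 weeks; 44/52 = 85%

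So scheduled collection looks back over about 8/52 = 15% to 12/52 = 23% of the year. The documents give no event rate for this population, so the number of events missed cannot be calculated from them.

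**The case against.** The strongest reply is that the harms section sets no attribution condition on the checklist. It is a systematic screen by a trained assessor for possible AEs, and the question wording elsewhere is labelled as examples from an instrument that is not shown. This stands in part. One cannot say that events are recorded only when someone already blames the treatment. But the harms section sends the reader to that description for detail, and the questions shown there presuppose a link, so the two still need reconciling.

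The second reply concerns serious events. A reader might infer that an unrelated hospitalization or death has no way into the data. The documents do not support that. The 48-hour rule has no relatedness condition and no end date, assessors speak to participants at both follow-ups, and people who stop treatment are still contacted. What remains is that the rule governs reporting once an event is known, and no scheduled question makes it known.

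Third, the harms named for the sleep components are short-term and come from components shared by both arms, so a check at post-treatment suits that risk. This is fair for those harms, but the promise covers all AEs.

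Three further readings are tempting and should not be drawn:

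- *Serious-event counts over 12 months are promised.* They are not. The DSMB section gives no window per participant.
- *The patient or therapist decides relatedness.* No one is named. The patient's reasons may only inform a later judgement, and a condensed article may leave the adjudicator to the full protocol.
- *The filter works differently by arm, because better memory for treatment helps a participant link a symptom to it.* The background says "The intervention was designed to improve memory for treatment contents rather than to improve general memory functioning", which makes the idea conceivable. But nothing in the documents shows that attribution differs by arm, the checklist prompts with named symptoms, and the article states no between-arm AE comparison.

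**Conclusion.** The point holds as a conflict between what is promised and what is collected. Followed as written, the plan cannot deliver a complete set of AEs classed as related or not related, or complete counts to the DSMB, and what it does deliver will be partly filtered by attribution. About 40 to 44 of 52 weeks (77% to 85%) have no scheduled AE question, only passive reporting of unexpected SAEs. This is a matter of completeness: many events, including serious ones, can still be captured.

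The conclusion rests on three assumptions: that post-treatment falls at weeks 8 to 12, which the article calls typical; that the example questions are representative of the checklist; and that no fuller safety procedure outside the article adds AE questions at follow-up. If the full instrument proves to be cause-neutral, the checklist part of the concern falls away. The therapist wording and the empty follow-up columns would remain.

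**What to change.** Reconcile the Adverse events section, {21a} and {22}, preferably by changing collection:

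1. Use a cause-neutral opening question covering any new or worse symptom or health event, with fixed items for hospital admission and other serious events.
2. Record the participant's own attribution as a separate field, so that it does not determine whether the event is logged.
3. Add the question to Table 2 at the existing 6- and 12-month calls.
4. For participants already assessed with the present wording, report AE results by checklist version.

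If collection stays as it is, restate {22} to say that the publication will cover AEs elicited by the checklist and treatment-related AEs up to post-treatment, plus SAEs that become known. The DSMB counts in {21a} should carry the same description.

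The cost is a wording change, two more marks in Table 2 and a few minutes at calls that take place anyway. The downsides are more unrelated events to log and partial non-comparability with early participants. Recruitment is stated to run from September 2023 through October 2026, so later participants, and earlier ones still in follow-up, would benefit.
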